## Abstract

**Background:**

Social anxiety disorder (SAD) has a high prevalence and an early onset with recovery taking decades to occur. Current evidence supports the efficacy of cognitive behavioral therapy (CBT) with virtual reality (VR) exposure. However, the evidence is based on a sparse number of studies with predominantly small sample sizes. There is a need for more trials investigating the optimal way of applying VR based exposure for SAD. In this trial, we will test the efficacy of CBT with adaptive VR exposure allowing adjustment of the exposure based on real-time monitoring of the participants's anxiety level.

**Methods:**

The trial is a randomized controlled, assessor-blinded, parallel-group superiority trail. The study has two arms: (1) CBT including exposure *in vivo* (CBT-Exp), (2) CBT including exposure therapy using individually tailored VR-content and a system to track anxiety levels (CBT-ExpVR). Treatment is individual, manual-based and consists of 10 weekly sessions with a duration of 60 min. The study includes 90 participants diagnosed with SAD. Assessments are carried out pre-treatment, mid-treatment and at follow-up (6 and 12 months). The primary outcome is the mean score on the Social Interaction Anxiety Scale (SIAS) with the primary endpoint being post-treatment.

**Discussion:**

The study adds to the existing knowledge by assessing the efficacy of CBT with adaptive VR exposure. The study has high methodological rigor using a randomized controlled trial with a large sample size that includes follow-up data and validated measures for social anxiety outcomes.

**Clinical trial registration:**

ClinicalTrials.gov, identifier: NCT05302518.

## Introduction

Social anxiety disorder (SAD) is a common anxiety disorder characterized by excessive fear of being scrutinized or criticized by others leading to avoidance of social situations (1). According to the ICD-10 classification of mental and behavioral disorders, engaging in feared situations is accompanied by autonomic symptoms of anxiety such as sweating, trembling or increased heartrate (HR). The lifetime prevalence of SAD ranges between 8.4 and 12.1% and the 12 month prevalence ranges between 4.2 and 7.1% (2, 3).

The avoidance of social interaction affects both work and personal life (4). Several social situations may be avoided because of excessive fear, such as small talk with peers or relatives, attending a job interview, expressing opinions or giving a presentation at work (4). Social anxiety may occur as a consequence of having high standards for one's own performance in social situations or having a wish to present oneself in a desired way combined with a lack of confidence in achieving these standards or making the right impression (5).

SAD is related to reduced health-related quality of life (6) and is also associated with substantial psychiatric comorbidity including other anxiety disorders, mood disorders and substance use disorders (3, 7). Epidemiological studies show that SAD most often precedes depression and that SAD is related to a substantial and consistent increase in risk of subsequent depression (8). Similarly, symptoms of social anxiety often precedes alcohol dependence (7).

SAD is an adolescent-onset disorder with a long recovery period (3, 8). Despite the prolonged recovery, few individuals with SAD seek treatment for their disorder. Only about one-third of lifetime cases report ever seeking treatment for SAD (3). Not seeking treatment may be related to the nature of the disorder itself. Individuals with SAD avoid treatment because the treatment itself constitutes a social situation that provokes anxiety (9).

### Treatment

The treatment of choice for social anxiety is cognitive behavioral therapy (CBT) (4). Treatment is conducted both individually and in group-settings. Exposure therapy is central to CBT and is very effective in fear reduction (10). Different theoretical approaches to cognitive behavioral therapy and exposure therapy exist; including inhibitory learning and emotional processing theory (11, 12). The inhibitory learning paradigm emphasizes exposure therapy which provides a foundation for learning alternative contingency rules competing with the conditioned fear response related to social situations (11). Emotional processing theory stresses the importance of habituation happening as a results of exposure as the driving mechanism leading to improvements in treatment (12).

A prominent cognitive behavioral model for SAD is the one proposed by Clark and Wells (13). According to their model, SAD is maintained by cognitive processes in addition to certain strategies and behaviors applied by the individual with SAD, including safety behaviors, inner focus of attention, anticipatory and post-event processing, and dysfunctional assumptions. Therapy focuses on addressing these maintaining factors and therefore therapy makes extensive use of behavioral experiments including in session role-play and *in vivo* exposure during sessions or conducted as homework assignments between sessions.

*In vivo* exposure is effective when treating SAD (14), but conducting *in vivo* exposure in session can be challenging because relevant social situations might be difficult to obtain and control. In addition, finding the right setting for exposure can be time consuming and costly (15, 16).

### Virtual reality and exposure-based therapy

Virtual reality computer-generated environments or 360° videos presented in a head mounted display that interacts with head movement creates the illusion of being able to look and move around in a virtual world. In 360° videos, the participant is immersed in a spherical video with 3 degrees of freedom (DoF). The interaction with head movement in 360° videos is constrained to rotation about the three perpendicular axes (pitch, yaw and roll) (17). Whereas, computer-generated environments may have 6 DoF making also translational movement possible in VR (i.e., moving forward/backward, up/down, left/right) (17). Hand controllers may further add to the immersive qualities of rendered environments by enabling interaction with the virtual environment.

VR has been used for exposure across different anxiety disorders and generally, there is no evidence that VR exposure is less efficacious than exposure *in vivo* (18–20). Exposure in virtual reality has several advantages compared to *in vivo* exposure. Virtual reality provides readily available environments for exposure, such as a meeting room with a group of people waiting for the patient to give a presentation. Furthermore, exposure in VR is highly controllable and can be modified to fit the needs of the patient. Finally, exposure takes place confidentially within the safety of the therapy room and thus the threshold for initiating exposure might be lower than for *in vivo* exposure.

A handful of randomized controlled trials (RCT) have implemented virtual reality exposure as part of the treatment for SAD (21–24) and for public speaking anxiety (25). Overall, the studies show that CBT with exposure in VR has a superior effect compared to waitlist control, and similar effect when compared to CBT with *in vivo* exposure. However, one study by Bouchard et al. was able to show, that exposure in VR was superior to *in vivo* exposure when embedded in CBT leading them to conclude, that VR-exposure embedded in CBT is an efficient and cost-effective way to treat SAD (22). Generally, the RCTs suffer from small sample sizes, with one larger study having 97 participants, but most studies being smaller having between 69 and 45 participants. There is a need for more RCTs investigating the effect of VR-exposure, especially larger RCT's.

Several meta-analyses on VR-exposure for SAD have been conducted (19, 26–30). Post-treatment the effect of CBT with VR-exposure is significant when compared to waitlist control, and the effect size is around g = 0.80. Whereas, the difference between CBT with VR-exposure and CBT with *in vivo* exposure is insignificant with effect sized ranging between g = 0.07 and g = −0.27.

### Psychophysiological measures in an adaptive treatment

Adaptive virtual scenarios may show additional clinical benefits by giving the therapist increased control in regulating the intensity of the exposure according to current anxiety levels (31–33). However, the effect of adaptive virtual scenarios applied in therapy remains largely unexplored (31). Real time assessment of anxiety level based on physiological measures may provide an essential aid in the therapist decisions on the progression of the exposure treatment (32). Detecting anxiety using psychophysiological measures has the advantage that it enables frequent assessment without disturbing the participants' sense of presence in VR (the illusion of being *there*) (34). Moreover, psychophysiological measures reflect involuntary reactions of the body, and are difficult to mask (35).

Psychophysiological measures such as electrodermal activity (EDA) and electrocardiogram (ECG) or photoplethysmograph (PPG) can be used to estimate anxiety in real time during exposure (32). EDA measures the changes in skin conductance that changes due to eccrine sweat production. Eccrine sweating reflects the sympathetic activity of the autonomic nervous system (ANS) and happens in the response to emotional stimuli like stress, anxiety, fear or pain (36). ECG or PPG can be used to measure HR. Parasympathetic and sympathetic activity of the ANS both affect the HR. Increased levels of sympathetic activity results in higher levels of HR. Like eccrine sweating, HR are used in emotion detection (35).

Using data derived from measures of EDA and PPG Petrescu et al. were able to predict low, medium and high levels of anxiety in real-time during exposure for heights (32). They developed a regression model utilizing different variables derived from EDA and PPG. Assessing anxiety levels using Subjective Units of Distress Scale (SUDS) they obtained a high accuracy between estimated anxiety, and actual anxiety levels (e.g., SUDS score), with an accuracy ranging between 69.52 and 90.48%.

There is a need for more trials investigating the optimal way of applying VR-exposure for SAD. The study described in the present protocol adds to the existing knowledge by assessing the efficacy of adaptive VR-exposure. Estimating anxiety levels based on psychophysiological measures provides the therapist the opportunity to increase or decrease the intensity of the exposure ensuring that intensity of the exposure is optimal. Thus, adaptive VR-exposure may provide additional clinical benefits compared to regular VR-exposure. The study is having high methodological rigor by being a RCT with a large sample size that includes follow-up data and well-validated measures for social anxiety outcomes and follows the SPIRIT guidelines for high quality RCTs (37).

### Objectives and hypotheses

In participants diagnosed with SAD, we aim to compare the effect of CBT including exposure therapy using individually tailored VR-content and a system to track anxiety levels (CBT-ExpVR) to CBT including exposure *in vivo* (CBT-Exp). Both treatments will be conducted as individual therapy.

#### Primary hypothesis

At post treatment we expect that CBT including exposure therapy using individually tailored VR-content and a system to track anxiety levels (CBT-ExpVR) will result in lower levels of social anxiety than CBT with exposure *in vivo* (CBT-Exp). The outcome on social anxiety will be measured using the total score on Social Interaction Anxiety Scale (SIAS).

#### Secondary hypotheses

At 6 and 12 months follow-up, we expect that VR-treatment will result in lower levels of social anxiety than *in vivo*-treatment.Post treatment and at 6 and 12 months follow up we expect that VR-treatment will result in lower levels of depression and higher levels of self-rated health than *in vivo*-treatment.The dropout rate we expect will be lower for the VR-treatment compared to the *in vivo*-treatment.

In addition to the evaluation of effect, a health economic evaluation will be made from a societal perspective.

## Methods

This protocol is written in accordance with SPIRIT 2013 (37, 38) and the TIDieR checklist and guide (39).

### Design

The trial is a randomized controlled, assessor-blinded, parallel-group superiority trail. The study is conducted at the Center for Digital Psychiatry in the Mental Health Services in the Region of Southern Denmark. Participants are randomly assigned to two different conditions: 1) CBT-ExpVR and 2) CBT-Exp. Both conditions offer a 10-week program with weekly one-hour sessions.

### Participants and recruitment

Participants will be recruited from the whole country but primarily from the Region of Southern Denmark. Different strategies will be used for recruitment including online advertisements (Facebook, Instagram, Twitter, LinkedIn, the Center for Digital Psychiatry's homepage, Sundhed.dk, and the project's own website), newspaper ads in addition to flyers and/or posters distributed at upper secondary schools, higher education, drop-in centers, and clinics of general practitioners.

Participants are referred to the trial's website where they are provided with written information about the study and are invited to complete online questionnaires screening for social anxiety symptoms and symptoms of depression. The questionnaire consists of SIAS and Major Depression Inventory and questions on current treatment and use of medication. Cut-off score for inclusion is <22 on SIAS (40, 41) and cut-off score for exclusion on MDI is <29. The online questionnaire might be supplemented by phone calls to inquire further information on current treatment and medication. No information will be obtained from patient records.

Eligible participants are invited to an assessment at the Center for Digital Psychiatry. Before the assessment, participants will receive thorough verbal information about the participation in the trial from one of the psychologists responsible for the treatment. At the assessment the participant will have the opportunity to bring a person of his or her own choice. The assessment will be carried out using the short version of the Present State Examination (PSE). At the assessment participants will be questioned on their use of medication, especially if they use any prescribed medicine that may affect HR or eccrine sweat production. Difficult cases will be discussed with a supervisor and/or at a weekly clinical conference before the diagnosis is made. Participants who meet the inclusion criteria will be offered to participate in the study. Participants who do not meet the inclusion criteria for the study and need treatment are recommended to contact their general practitioner as well as other available resources. Before the pre-treatment assessment, included participants will be asked to complete an informed consent form. With information about the trail provided at the diagnostic interview participant will have more than the 24 h to consider whether to enroll in the study or not. Figure 1 provides an overview of the recruitment process, interventions, and assessment.

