### Exclusion criteria

Previously diagnosed with autism spectrum disorders.Previously diagnosed with psychotic disorders.Severe depression (>29 MDI).Dependence syndrome according to ICD-10 classification of mental and behavioral disorders (F1x.2) (1).Suicidal ideation.Dementia/Intellectual disability.Epilepsy.Taking part in other kinds of psychological intervention for SAD.Medication (SSRI, benzodiazepine, MAOI) type and doses needs to be stable three months prior to inclusions and during the intervention.

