### Sample size

A recent study reported ~10-point drop in SIAS for standard treatment and 20-point drop for traditional VR-exposure with standard deviations around 15 points (22). With adaptive/tailored VR-exposure we find it reasonable to assume a similar effect size (d = 0.66 and 1.33, respectively). The standard variation is between participants, which we expect to be conservative for our paired design. Using the measurement error based on test-retest reliability of the SIAS a drop of 13 points is considered a statistical reliable change (41). Meta-analyses have indicated smaller effect sizes, but the analyses are still based on rather few RCTs, which did not benefit from the improvements we propose in this study. If 35 participants are recruited for each group, this will lead to a statistical power of 0.80 comparing the VR-treatment to in vivo-treatment at the 0.05 significance level. To consider a 20% dropout we plan to invite 90 participants in total.

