### Assessment

#### Primary outcome measure

SIAS measured at pre-treatment, mid-treatment, post-treatment and at follow-up (6 and 12 months). The instrument is a measure of social anxiety symptoms and consists of 20 items assessing cognitive, affective, and behavioral responses to social interaction. In a comparison of social phobia outcome measures Cox et al. found strong support for SIAS which showed good sensitivity to treatment effects (49). The scale ranges from 0 to 80. Participants have to indicate to what degree they feel each statement is characteristic to them using a 5-point Likert scale (0 = not at all, 1 = slightly, 2 = moderately, 3 = very, 4 = extremely). The instrument has high internal consistency, Cronbach's alpha = 0.93, and high test-retest reliability, r = 0.92 (50).

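### Both inequality signs in the online screening rule are reversed: the MDI sign contradicts the exclusion criteria, and the SIAS sign runs against the scale and the target population

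*Protocol article*

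**What the plan says.** The protocol article describes entry in two steps. Under Participants and recruitment, volunteers complete an online questionnaire containing the SIAS and the MDI, and the rule applied to it is "Cut-off score for inclusion is <22 on SIAS (40, 41) and cut-off score for exclusion on MDI is <29". Those found eligible are then invited to an assessment with the Present State Examination.

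The formal lists follow. Inclusion criteria asks for age, language and an ICD-10 diagnosis of social anxiety disorder (F40.1), and gives no SIAS threshold. Exclusion criteria contains "Severe depression (>29 MDI" as a reason for exclusion.

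The direction of the SIAS is given in two places. Under Primary outcome measure, "The scale ranges from 0 to 80" and the item responses are "0 = not at all, 1 = slightly, 2 = moderately, 3 = very, 4 = extremely". The primary hypothesis treats a lower SIAS score as the benefit: the VR arm "will result in lower levels of social anxiety than CBT with exposure" in vivo.

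**The concern.** The screening sentence is the only place in the text shown that gives a SIAS threshold for entry, so no correct statement elsewhere overrides it. For the MDI there is a second statement, and it says the opposite.

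The screen decides who is invited to assessment. Taken at face value, it turns away the people the trial is meant to study and, on the MDI, rejects those without severe depression. Anyone who has to apply the rule, audit eligibility, classify a protocol deviation or describe the trial population later needs one usable rule, and the text does not give one.

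**Working it through.** No figure in the plan is derived from these thresholds, so there is none to reproduce. The check is to apply each rule literally and compare it with the rest of the document.

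**MDI**

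- Participants and recruitment: "cut-off score for exclusion on MDI is <29". Reject if MDI < 29; those left have MDI ≥ 29.
- Exclusion criteria: "Severe depression (>29 MDI". Reject if MDI > 29; those left have MDI ≤ 29.
- Both together: MDI ≥ 29 and MDI ≤ 29, so MDI = 29 only. This does not depend on the upper end of the MDI range, which the article does not state.
- Which sign is out of line: the secondary outcome section describes the MDI as measuring depression severity, and the exclusion list attaches the severe label to scores above 29. Higher is therefore worse, and the recruitment sentence is the one that points the wrong way.

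**SIAS**

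- Direction: 20 items scored 0 to 4 give a maximum of 20 × 4 = 80, matching the stated range. Item labels run from not at all to extremely, and the primary hypothesis counts a lower total as better. Higher therefore means more social anxiety.
- Literal rule: "Cut-off score for inclusion is <22 on SIAS (40, 41") passes scores 0 to 21, which is 22 of the 81 possible scores, and turns away 22 to 80, the other 81 − 22 = 59.
- The passing group is thus the low end of the scale, while the trial population must hold a diagnosis of social anxiety disorder.

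**Effect of reversing both signs**

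| Rule | As written | Direction reversed | Still open |
|---|---|---|---|
| SIAS, proceed to assessment | 0 to 21 | above 22, or 22 and above | score of 22 |
| MDI, excluded | below 29 | above 29, or 29 and above | score of 29 |

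With the direction reversed, the SIAS rule fits the target population and the MDI rule agrees in direction with the exclusion criteria. The exclusion criteria as written admit a score of 29. The recruitment sentence does not settle either boundary once its signs are corrected.

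**Sample size**

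The calculation uses assumed drops of about 10 and 20 points and an SD of about 15; no screening threshold enters it. With a difference of 20 − 10 = 10 points, d = 10/15 = 0.667. At 35 per arm and two-sided 0.05 (two-sided is assumed here), power is 0.796 by the normal approximation and 0.785 by the t-test, close to the stated 0.80. Allowing for 20% dropout, 70/(1 − 0.20) = 87.5, rounded up to 88, against the planned 90. None of these figures changes when the signs are corrected.

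**The case against.** The strongest reply is that this is a notation slip that misleads nobody. Both signs in one sentence are flipped in the same way, the exclusion list gives the MDI direction with its label, and the diagnosis, scale and hypothesis make it plain that high SIAS scores are wanted. A rule leaving one admissible MDI score would nearly stop recruitment and be noticed at once. This stands as an account of how the error probably arose. It does not remove it: the sentence is current operative text, and for the SIAS it is the only threshold shown.

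One can also read the MDI clause loosely, as requiring a score below 29 to avoid exclusion. The wording calls it a cut-off for exclusion, so this is strained, and it still disagrees with the exclusion criteria at a score of exactly 29. No similar reading rescues the SIAS clause. The flowchart in Figure 1 is not shown, so it may or may not state the thresholds correctly.

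A reader might infer three stronger things, and the documents support none of them:

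- **The trial would enrol people with little social anxiety.** Screening only leads to an invitation. The Present State Examination and an ICD-10 diagnosis still stand between the screen and enrolment. The literal harm is wrongly turning people away.
- **The planned effect becomes unattainable because nobody can drop more than 21 points.** The plan does assume a "20-point drop for traditional VR-exposure with standard deviations around 15 points", which sits badly with entry scores of 0 to 21. But the SIAS is measured again at pre-treatment, so the screening score does not strictly cap the baseline or the later change.
- **The online form was programmed with the wrong signs.** Nothing shown says how the rule was implemented. That REDCap holds the self-report data does not show that it applies the screening rule.

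**Conclusion.** The point holds as an error in the text that needs correction. Both inequalities in the screening sentence are reversed. The contradiction with the exclusion criteria concerns the MDI only, and there the two rules jointly admit one score, 29. The SIAS reversal is shown by the scale direction, the primary hypothesis and the required diagnosis, because neither criteria list contains a SIAS threshold. Read literally, the screen would pass 0 to 21 and turn away 22 to 80 before assessment.

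The conclusion assumes that the signs printed in the article are those in force. It makes no claim about who was actually screened in or out, and none about the power of the trial.

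**What to change.** In Participants and recruitment, correct the direction of both signs so that higher SIAS scores proceed to assessment and the MDI exclusion agrees with the exclusion criteria. The sponsor should state on which side a SIAS score of exactly 22 and an MDI score of exactly 29 fall; the documents do not settle the SIAS boundary, and the MDI boundary should read the same in both sections. The sponsor should also confirm that the screening actually applied to volunteers matches the corrected text, and report it if it did not.

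The cost is one corrected sentence and one check of the screening procedure. No analysis, sample size or schedule changes.
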